
#### 2.10.4. Black Box

The “black box” used to establish blinding, is a professionally manufactured plastic box with metal components capable of encapsulating either the adsorber cartridge (intervention) or a regular tube in case of the control group (CytoLock^®^ System, Jena, Germany, Figure 2 and Figure 3). This plastic box meets all the hygiene requirements of our ICU and does not cause any dysfunction of the ECMO circuit. Tubing going in and out of the box are identical in length, appearance and cannot be pushed in or pulled out regardless of group allocation. To avoid kinking of the tubing in the proximity of the box, a customized guiding contraption has been fitted.

### 2.11. Safety, Possible Complications, Risks

Study participation will not be associated and/or expected with any additional risks for a patient’s safety.

The safety of the adsorber will be evaluated on both clinical and device–based parameters. Clinical parameters will include the occurrence of (severe) adverse device effects, the monitoring of vital signs, and clinical laboratory changes. Device-specific parameters will include the incidence of any device related technical issues that may adversely affect treatment, e.g., critical changes in pressure profiles of the extracorporeal circuit, that may be caused by obstructions, leaks or breaks, or any other physical failures of the device. The adsorber will not be used if it appears to be damaged, and if beads appear to be free floating within the endcaps.

Patients will be monitored for clinical events associated with extracorporeal treatment. Documentation of relevant events regarding the adsorber (CytoSorb^®^) includes but is not limited to: periprocedural complications within 30 days combined from (pericardial effusion, stroke, major bleeding, embolization, intracranial bleeding), device related (thrombus, breakage, malfunction, allergic reactions), air embolism, technical and procedural success of device implantation and severe hypotension.

Events which are not plausibly explainable by the underlying disease (cardiogenic shock) or a known comorbidity or if the event is considered or suspected to have a causal relationship to the adsorber are classified as adverse events. The definitions are based on the new Medical Device Regulation (EU) 2017/745.

In compliance with Article 2, Number 58 of the Medical Device Regulation (MDR), a serious adverse event (SAE) refers to any adverse event that resulted in one or more of the following outcomes: death; serious deterioration in the subject’s health leading to a life-threatening illness or injury, permanent impairment of a body structure or function, hospitalization or prolonged hospitalization, medical or surgical intervention to prevent life-threatening illness or injury, or permanent impairment of a body structure or function; and the development of a chronic disease.

It should be noted that planned hospitalization for a pre-existing condition or a procedure required by the study protocol, without any serious deterioration in health, is not considered a serious adverse event. These criteria ensure the comprehensive assessment and reporting of adverse events throughout the study.

Occurrences will be systematically documented from the time of study inclusion and throughout the follow–up period, which extends up to day 30 after the commencement of implantation. In case of an emergency within the intervention phase (first 72 h after implantation) that requires the knowledge of the treatment arm of the patient, the black box will be opened, and the respective device will be removed if an adverse effect of the adsorber is suspected. In case an unblinding is needed after the 72 h intervention phase has passed, an unblinding list will be used to find out in which arm the patient is classified. The integrity of all bloodlines and connections prior to the initiation and periodically during the treatment will be checked by a perfusionist and by the treating ICU team. To avoid any kind of air embolism, we use a priming set for the cartridge.

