#### 2.12.2. Statistics

The primary outcome analysis will involve comparing the experimental group receiving CytoSorb^®^ with the control group receiving standard care (without CytoSorb^®^), focusing on the differences in the mean Inotropic Score (IS) at 72 h post-implantation. The primary analysis will encompass the full analysis set, including all patients who were randomized and received treatment, following the intent-to-treat (ITT) principle. Sensitivity analyses are planned in the per-protocol (PP) analysis set. A linear model will be fitted for the primary endpoint with treatment and baseline IS as fixed effects. The confirmatory analysis will be performed at a significance level of 5%. The mean difference of the primary endpoint will be estimated within the model and will be reported with 95% confidence interval. Categorical endpoints will be compared by Chi-square test/Fisher’s exact test between groups. According to the data distribution, two-sided independent samples *t* test or Mann–Whitney U test will be applied for continuous endpoints. Adequate descriptive statistics will be used to summarize the data in each group. All secondary analyses will be performed exploratively, i.e., without adjustment for multiplicity. Safety analyses will be run in the safety population to be defined in the protocol; these analyses will summarize and tabulate all observed safety events including a measure of uncertainty (i.e., 95% confidence intervals).

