**Diagnostic procedures**							
12-lead surface ECG ^∆^	X		X	X	X		
TTE ^∆^	X		X	X	X	X	
Technical data from ECMO ^∆^	X			X	X	X	
Laboratory evaluation ^∆^	X		X	X	X	X	
Local blood chemistry ^∆^	X		X	X	X		
PAC–Hemodynamics ^∆^	X			X	X		
Measurement of parameters of hemodynamics ^∆^	X		X	X	X	X	
Measurement of mortality ^∆^	X					X	X
Measurement of duration of ECMO, ventilation, dialysis, inotropic therapy ^∆^	X			X	X	X	X
Measurement of the neurological outcome ^∆^	X			X	X	X	X
VA–ECMO Implantation	X			X			

^∆^ Data documentation from clinical routine (if available). * Recording of AEs/SAEs after implantation of CytoSorb® adsorber or ECMO tube, ^†^ device = either CytoSorb^®^ adsorber (= intervention group) or ECMO tube (= control group) via black box. ^1^ within the first 6 h after implantation of VA-ECMO, ^2^ changed every 24 h within the intervention of 72 h, V = visit, mRS = modified Rankin Scale, SAPS = Simplified Acute Physiology Score, APACHE = Acute Physiology And Chronic Health Evaluation, SOFA = sepsis-related/sequential organ failure assessment score, ECG = electrocardiography, TTE = transthoracic echocardiogram, ECMO = Extracorporeal membrane oxygenation, PAC = pulmonary artery catheterization, VAS = visual analogue scale, h = hours.

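### The adverse event definition filters events by presumed cause, so deaths and complications put down to the shock can be missing from the AE and SAE tables

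*Protocol article*

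**What the plan says.** Section 2.11 gives two routes by which an event becomes an adverse event. The first is that it belongs to "Events which are not plausibly explainable by the underlying disease (cardiogenic shock) or a known comorbidity". The second is that the adsorber is suspected: "or if the event is considered or suspected to have a causal relationship to the adsorber are classified as adverse events". The serious category is built on top of this: "a serious adverse event (SAE) refers to any adverse event that resulted in one or more of the following outcomes: death", followed by the other serious outcomes. The section then concludes: "These criteria ensure the comprehensive assessment and reporting of adverse events throughout the study".

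The same section separately lists events to be documented, beginning with "periprocedural complications within 30 days combined from (pericardial effusion, stroke, major bleeding, embolization, intracranial bleeding" and continuing with device-related events, air embolism and severe hypotension. That sentence carries no condition on presumed cause. Section 2.12.2 says of the safety population that "these analyses will summarize and tabulate all observed safety events", with 95% confidence intervals.

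The start of recording is given in two ways. Section 2.11 says "Occurrences will be systematically documented from the time of study inclusion and throughout the follow–up period". The footnote to Table 1 says "Recording of AEs/SAEs after implantation of" the adsorber or the ECMO tube.

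**The concern.** A randomised control arm makes it possible to detect device harm without deciding the cause of any single event: count events in each arm and compare. The definition in section 2.11 puts a causality judgement before that count. In cardiogenic shock on VA-ECMO, many serious events can plausibly be put down to the underlying disease. An adsorber effect that looks like the disease is the kind that case-by-case attribution will miss and that only an unfiltered comparison of arms would show.

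The second route gives limited help. Section 2.1 says that only the perfusionist knows the allocation, so the treating team has little basis for suspecting the adsorber when an event resembles shock.

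At stake is whether the AE and SAE tables can be read as a full account of what happened in each arm. There is also a smaller inconsistency: events between study inclusion and connection of the device are in or out depending on whether section 2.11 or the Table 1 footnote is followed.

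**Working it through.** **Inputs from the protocol article**
- Arm size: 54 randomised, 27 per arm (section 2.12.1).
- ICU mortality of the site's ECMO patients: about 80% (section 3). The Introduction cites survival of 20% to 30% with VA-ECMO, i.e. mortality of 70% to 80%.
- Share of events judged explainable by shock or a comorbidity: not given. Assumed range: 50% to 95%.

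**The plan's own figure.** The article gives no figure for the safety comparison. The sample size supplies only the number per arm, and it reproduces: a two-sided t test with a difference of 5 and SD 5.6 needs 20.7, so 21 per arm (power 80.6%). With 20% dropout, 21 / 0.8 = 26.25, so 27 per arm and 54 in total.

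**Step 1: following the definitions.** Take a death that blinded clinicians put down to the shock.
1. It is plausibly explainable by the underlying disease, so the first route does not apply.
2. The adsorber is not suspected, so the second route does not apply.
3. It is therefore not an adverse event.
4. An SAE is a subset of adverse events, so it is not an SAE either.

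**Step 2: deaths that would still count as SAEs.** Formula: 54 × mortality × (1 − share judged explainable).

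| Share judged explainable (assumed) | Mortality 80%: 54 × 0.8 = 43.2 deaths | Mortality 70%: 54 × 0.7 = 37.8 deaths |
|---|---|---|
| 50% | 21.6 | 18.9 |
| 75% | 10.8 | 9.4 |
| 90% | 4.3 | 3.8 |
| 95% | 2.2 | 1.9 |

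**Step 3: effect on a comparison of arms.** Take a complication that reaches the tables only through the AE definition, with assumed true rates of 20% and 50%, 27 per arm, and the same share filtered out of each arm. The recorded rate is the true rate × (1 − share).

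| Share filtered (assumed) | Recorded rates | Difference | Power |
|---|---|---|---|
| 0% | 20% vs 50% | 30 points | 64% |
| 50% | 10% vs 25% | 15 points | 30% |
| 75% | 5% vs 12.5% | 7.5 points | 16% |
| 90% | 2% vs 5% | 3 points | 9% |

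The ratio of rates stays at 2.5 in every row. The absolute difference and the ability to see it both shrink.

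**Step 4: what escapes the filter.**
- Section 2.7.2 defines 30-day mortality without restriction by cause, and includes the incidence of stroke.
- The list in section 2.11 covers stroke, major and intracranial bleeding, embolization, pericardial effusion, device-related events, air embolism and severe hypotension.
- The Abstract names peripheral ischemic and vascular complications among the safety endpoints. These two are not in the section 2.11 list, although that list is expressly open-ended.

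**The case against.** A reader might infer that most deaths and many complications drop out of the between-arm comparison altogether. The document does not support that. Mortality at 30 days is a secondary endpoint regardless of cause, Table 1 schedules its measurement at V2 and V3, and section 2.12.2 compares categorical endpoints between groups. Stroke, major bleeding and severe hypotension are listed for documentation with no condition on cause. Organ function is followed through SOFA, kidney markers and duration of renal replacement therapy. This part of the objection stands, and it confines the loss mainly to the AE/SAE tables and to events on none of these lists.

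A reader might also infer a bias toward one arm. With blinded attribution the filter should act about equally in both arms, so that reading is not supported either. Emergency opening of the black box during the first 72 h is the exception, because attribution after that point is no longer blinded.

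It can further be said that section 2.12.2 speaks of safety events, not adverse events, and so may already mean the unfiltered set. That is a possible reading, but the text does not say so. The article does condense a fuller protocol, and detail left to that protocol is no finding. The plausibility condition, however, is a rule the article states, not a detail it omits.

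On the start of recording, section 2.7.1 treats randomisation and implantation as one time point, and the device is connected within 6 h of ECMO implantation. The affected window is therefore short. The two statements still differ.

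**Conclusion.** The point holds in a limited form. Followed as written, the definition in section 2.11 lets deaths and complications attributed to shock go unrecorded as AEs or SAEs. This contradicts the comprehensive reporting that the same section claims, and it leaves the scope of the safety tables in section 2.12.2 open. The consequence is lost events and diluted absolute differences in the AE/SAE tables, mainly for events not collected elsewhere.

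The size is unknown. The range of about 22 down to 2 deaths counted as SAEs, out of about 43, rests on two assumptions: that trial patients die at the site's ICU rate of about 80%, and that 50% to 95% of deaths are judged explainable by shock. The complication rates in the working are illustrative only. The mismatch in the start of recording is real but minor.

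**What to change.** 1. In section 2.11, remove the plausibility condition from the classification of adverse events.
2. Record all deaths, all serious events and all listed safety events (those in section 2.11 and in the Abstract) in both arms, whatever the presumed cause.
3. Keep relatedness to the adsorber as a separate attribute, judged blind to allocation, that does not decide whether an event is recorded.
4. In section 2.12.2, state that the safety analysis tabulates this unfiltered set by arm, including all deaths.
5. Reconcile section 2.11 and the Table 1 footnote to one start of recording common to both arms, such as randomisation.

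These changes affect recording and tabulation only. The cost is a wording amendment and some additional event forms in a very sick population. The burden is contained because much of the information is already collected for the secondary endpoints and the listed complications.

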### 2.12. Statistical Considerations and Methods

#### 2.12.1. Sample Size

Sample size calculation was conducted for the primary outcome of Inotropic Score (IS) at 72 h following CytoSorb^®^ or tube implantation. The estimated sample size is based on the standard deviation (SD) of the inotropic score after 72 h from our own VA–ECMO patient population (SD = 5.6). To detect a difference of 5 points in the IS score between both groups with a power of 80%, a total of 44 patients (21 per group) need to be analyzed (two-sided independent samples t test, α = 0.05). Considering an anticipated dropout rate of 20%, the trial aims to recruit 54 patients, with 27 patients assigned to each group.

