### 2.7. Endpoints

#### 2.7.1. Primary Endpoint

The primary endpoint of the ECMOsorb trial is the mean difference of the Inotropic Score (IS) 72 h after randomization (implantation of CytoSorb^®^ or a normal ECMO tube) between the two study arms. The Inotropic Score is calculated as: dopamine dose [μg/kg/min] + dobutamine dose [μg/kg/min] + 100xepinephrine dose [μg/kg/min] + 100× norepinephrine [μg/kg/min].

The role of dopamine in the management of cardiogenic shock remains a topic of debate. It has been observed that the administration of dopamine is associated with an increased incidence of arrhythmic events and higher mortality rates among patients with cardiogenic shock [27,28]. As a result, dopamine is not included in the repertoire of inotropic agents and vasopressors employed for the treatment of acute heart failure at our study site.

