## 3. Discussion

Despite the growing utilization of ECMO in various life-threatening acute conditions [12,30,31,32], significant progress in the field of mechanical circulatory support and critical care, the rates of morbidity and mortality among ECMO patients continue to be alarmingly high [12]. The ICU mortality rate for our ECMO patients is approximately 80%.

The effectiveness of CytoSorb^®^ remains a subject of controversy [33]. Triple-blinded, randomized trials investigating the acute hemodynamic, echocardiographic, immunological, and cellular effects of VA-ECMO with the concurrent use of an adsorber to mitigate or potentially prevent an associated inflammatory response in patients with cardiogenic shock have not yet been conducted. ECMOsorb aims to assess the effectiveness of CytoSorb^®^ through a triple-blinded, randomized trial involving a larger cohort of patients with cardiogenic shock and VA-ECMO. The trial will focus on evaluating a clinical endpoint associated with hemodynamic improvement. Establishing efficacy would represent an initial evidence-based advancement for this challenging patient population that is often difficult to treat.

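### Section 2.12.1 requires 44 analysed patients but 21 per group; two groups of 21 make 42, which is what the stated inputs give

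*Protocol article*

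**What the plan says.** Section 2.7.1 defines the primary endpoint as "the mean difference of the Inotropic Score (IS) 72 h after randomization" between the two arms. Section 2.12.1 sizes the trial on that endpoint. It takes an SD of 5.6 from the site's own VA-ECMO patients and aims "To detect a difference of 5 points in the IS score between both groups" at 80% power, with a "two-sided independent samples t test, α = 0.05". It concludes that "a total of 44 patients (21 per group) need to be analyzed". It then adds the loss allowance: "Considering an anticipated dropout rate of 20%, the trial aims to recruit 54 patients, with 27 patients assigned to each group". Section 2.4 fixes allocation at 1:1.

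Two other places bear on the query. Section 2.12.2 analyses all randomised and treated patients with a linear model containing treatment and baseline score; it does not say what value a patient who dies before 72 h receives. The Discussion (section 3) states: "The ICU mortality rate for our ECMO patients is approximately 80"%. It attaches no time point to that figure, and the article gives no mortality by 72 h.

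**The concern.** The number of patients who must be analysed is the benchmark for judging whether the trial met its design, and one sentence gives it two values. Read as 42, the planned recruitment meets it at the planned loss. Read as 44, the planned recruitment falls just short of it. A reader cannot tell from the sentence alone which applies.

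The margin for loss is also narrow, and the endpoint is measured at 72 h in a population with high mortality. It is therefore useful to know how many missing 72 h scores the design can absorb, a figure the paragraph does not give.

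**Working it through.** **Inputs (section 2.12.1):** difference 5; SD 5.6; two-sided alpha 0.05; power 80%; independent-samples t test; dropout 20%; 54 recruited, 27 per group. Allocation 1:1 (section 2.4).

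**Step 1. Evaluable number.** The standardised difference is 5/5.6 = 0.893. For n per group, the t test has 2n − 2 degrees of freedom and noncentrality 0.893 × √(n/2). Exact power from the noncentral t distribution:

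| n per group | Total | Noncentrality | Power |
|---|---|---|---|
| 20 | 40 | 2.82 | 78.6% |
| 21 | 42 | 2.89 | 80.6% |
| 22 | 44 | 2.96 | 82.5% |

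The solution is 20.7, so 21 per group is the smallest size reaching 80%. The plan's per-group figure is reproduced; its total is not, because 2 × 21 = 42.

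**Step 2. Recruitment target.**
- From 21 per group: 21/0.8 = 26.25, rounded up to 27 per group, 54 in total. This reproduces the plan.
- From 22 per group: 22/0.8 = 27.5, rounded up to 28 per group, 56 in total.
- Working back from 54: 54 × 0.8 = 43.2, which is above 42 and below 44.
- From 22 with the weaker multiplicative inflation: 22 × 1.2 = 26.4, rounded up to 27. This also gives 54, but it does not fully allow for 20% loss.

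**Step 3. Reserve for missing 72 h scores.** 54 − 42 = 12 patients, and 12/54 = 22.2%. With loss spread about evenly over the arms, t-test power from 54 randomised is:

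| Loss | Evaluable | Power |
|---|---|---|
| 20% (stated) | 43.2 | 82% |
| 30% (assumed) | 37.8 | 76% |
| 40% (assumed) | 32.4 | 69% |

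The planned baseline adjustment would recover some of this. With an assumed correlation of 0.5 between baseline and 72 h scores, the SD falls to 5.6 × √(1 − 0.25) = 4.85, and 16 per group (about 40% loss) gives about 81%.

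**Step 4. What the 80% ICU mortality implies for 72 h.** The documents do not say. If early deaths counted as loss and nothing else were lost, the reserve would be used up once 22.2/80, or about 28%, of the ICU deaths fell before 72 h. Assuming a constant hazard with 80% dead by day T, mortality by day 3 is 1 − 0.2^(3/T): 15% for T = 30, 29% for T = 14, 38% for T = 10. The values of T are assumptions. The range lies on both sides of the 20% allowance, so it does not settle the matter.

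**The case against.** The strongest reply is that the slip has almost no consequence. 21 per group is right for the stated inputs, 54 follows from it, and correcting the total alters nothing else. Even against a requirement of 44, the shortfall at 20% loss is 0.8 of a patient, and power there is about 82%. This stands, and it limits the weight of the point. It does not remove the contradiction.

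A second reply is that 44 may have been intended, with 22 per group, since 22 × 1.2 also rounds up to 27. This stands as far as it goes: the figure 54 alone does not prove which total was meant. The stated inputs do favour 21, the smallest size that reaches 80%, and dividing by 0.8 is the correct allowance for 20% loss.

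A reader might go further and infer that, with 80% ICU mortality, the 20% allowance is too small and the stated power unsupported. The documents do not support that. The 80% covers an ICU stay of unstated length in the site's ECMO patients generally, whereas the endpoint is at 72 h and section 2.9 excludes several high-risk groups. Section 2.12.2 does not say that death before 72 h counts as loss, and an article may leave that, and the basis of the 20%, to the full protocol or analysis plan. What remains is a query.

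**Conclusion.** The point holds for the arithmetic. The total of 44 is inconsistent with 21 per group, and the stated inputs give 42, with power of 80.6%. This rests only on the article's own figures and the exact t-test calculation. The error is two patients in the stated requirement; recruitment of 54 is unaffected.

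The documents do not show that 80% power is missed: at the stated 20% loss it is about 82%. The limit of 12 missing scores applies to the unadjusted t test with loss roughly balanced between arms. The power figures at 30% and 40% loss illustrate assumed rates and are not forecasts.

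**What to change.** In section 2.12.1, state that 42 patients in total (21 per group) need to be analysed, giving power of 80.6%, and that 54 will be recruited. Add one sentence saying that 80% t-test power holds while no more than 12 of 54 patients (22%) lack a 72 h score. Should the sponsor confirm that 22 per group was intended, the per-group figure has to change instead, and the text should acknowledge that 54 less 20% leaves 43.2.

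As a query only: the sponsor holds the 72 h data behind the SD of 5.6 and should check from them whether the 20% covers deaths before 72 h, if these count as loss.

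The cost is wording. No change to enrolment is asked for.
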